To date, randomised controlled trials (RCT) examining the effectiveness and efficacy of NMBAs for paediatric ARDS are lacking. Our group found that continuous administration of NMBAs significantly improved oxygenation in patients with moderate-to-severe PARDS [12]. The Paediatric Acute Lung Injury Consensus Conference (PALICC) and the Paediatric European Mechanical Ventilation Consensus Conference (PEMVECC) recommended that clinical trials investigating the short- and long-term outcomes of NMBA use are much needed, especially as—despite the lack of evidence—NMBAs are often used in the most critically ill paediatric patients [13–18]. Furthermore, the possible beneficial effects of NMBAs must be outweighed against side-effects such as critical illness polyneuropathy and myopathy (CIPNM), a phenomenon that has been observed especially in adults who are on concurrent corticosteroids or have renal failure [19]. Limited data suggest the prevalence of CIPNM in children is very low [20].

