### Relevant concomitant care permitted or prohibited during the trial {11d}

Standard of care is provided for all enrolled patients. It is guided by clinical judgement, local guidelines, and international recommendations from PALICC and PEMVECC, and includes ventilator management, sedation and analgesia use, nutrition, transfusion management and hemodynamic and fluid management [17, 25]. Ventilator management goals are adequate oxygenation and ventilation, defined by pulse oximetry oxygen saturation (SpO_2_) 88–92% and 7.20 ≤ pH ≤ 7.35 (irrespective of PaCO_2_) during the acute phase of disease. PALICC recommendations include expiratory tidal volume (Vte) 5–7 ml/kg ideal body weight (IBW), peak inspiratory pressure (PIP) ≤ 28 cm H_2_O (may allow up to 32 cm H_2_O for patients with poor chest wall compliance, i.e. those with increased chest wall stiffness or increased abdominal pressure) and PEEP set by FiO_2_ and respiratory system mechanics. Use of pulmonary specific and non-specific ancillary treatment including inhaled nitric oxide (iNO), steroids, surfactant and prone positioning are also at the discretion of the local bedside team. Use of escalating interventions such as high-frequency oscilattory ventilation (HFOV) or ECLS is also at the discretion of the bedside team. Ventilation treatment failure is defined as a 4-h pattern of either persistent hypoxia (SaO_2_< 85%) with FiO_2_ 1.0 and max PEEP or persistent hypoventilation (pH < 7.20) with PIP > 35 cmH_2_O and a respiratory rate that does not cause intrinsic PEEP. Onset of weaning is at the discretion of the attending physician. Once deemed eligible for weaning, a daily extubation readiness test (ERT) is performed per institutional algorithm.

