### Outcomes {12}

#### Primary outcome measure

Cumulative respiratory morbidity score 12 months after PICU discharge, adjusted for confounding by age, gestational age, family history of asthma and/or allergy, season in which questionnaire was filled out, day-care and parental smoking.

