##### Exploratory outcome measures

These include use of (non-) pulmonary ancillary treatment (e.g. steroids, inhaled drugs, prone positioning) and HFOV, daily cumulative dosage sedatives and analgesics, prevalence of drug withdrawal symptoms and delirium, ventilator-free days at day 28 (VFD), length of MV, length of PICU stay and mortality. We will also explore changes in Pediatric Cerebral Performance Category and Pediatric Outcome Performance Category.

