## Assignment of interventions: Blinding

### Who will be blinded {17a}

Full blinding of the clinical team cannot be ensured because children randomised to the control arm may display spontaneous movements and/or breathing. For this reason, the study team will be prohibited from participating by any means in the clinical care of the participant. On top of that, the statistical analysis and long-term outcome assessment staff are blinded to the study arm, and aggregate outcome data will be restricted to an unblinded statistician and the data safety monitoring board.

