## Statistical methods

### Statistical methods for primary and secondary outcomes {20a}

Data is analysed with an intention-to-treat approach. The primary outcome measure is a continuous outcome parameter. First, it will be tested for normality using the Shapiro-Wilk test. Dependent upon the outcome of this test, in the univariate analysis, the primary outcome will be displayed as mean ± standard deviation or median (25–75 interquartile range) and analysed using either the Student *t* test or the Mann-Whitney *U* test. Paired analysis will be used to compare the primary outcome with its baseline value. In multivariate analysis, zero inflated regression analysis is used to adjust for possible confounding by age, gestational age, family history of asthma and/or allergy, season in which questionnaire was filled out, parental smoking, and parental perception of the outcome of randomisation. Depending on the outcome of the analysis on randomisation outcome, variables that were significantly different between the intervention and control arm will also be adjusted for in the multivariate analysis. On top of that, we will adjust if there is an imbalance in the use of (non-) pulmonary specific ancillary treatment used during PICU admission.

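### The multivariate model for the primary outcome adjusts for two variables that arise after randomisation, which can bias the intention-to-treat effect or cost power, and its covariate list is left to the data

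*Protocol article*

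**What the plan says.** Statistical methods for primary and secondary outcomes {20a} states an intention-to-treat approach. It plans an unadjusted comparison of the primary outcome (Student t or Mann-Whitney, depending on a normality test), then a zero-inflated regression. Three parts of that regression matter here:

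- The listed covariates end with "parental smoking, and parental perception of the outcome of randomisation".
- After the arms have been compared, "variables that were significantly different between the intervention and control arm will also be adjusted for in the multivariate analysis".
- Finally, "we will adjust if there is an imbalance in the use of (non-) pulmonary specific ancillary treatment used during PICU admission". No criterion for imbalance is given.

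The Primary outcome measure paragraph defines the endpoint itself as adjusted: "Cumulative respiratory morbidity score 12 months after PICU discharge, adjusted for confounding by age, gestational age, family history of asthma and/or allergy", followed by season of the questionnaire, day-care and parental smoking. Neither parental perception nor ancillary treatment is on that list. Day-care is on it but is missing from {20a}.

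Ancillary treatment is discretionary: under Relevant concomitant care {11d}, "steroids, surfactant and prone positioning are also at the discretion of the local bedside team". That team may know the arm: "Full blinding of the clinical team cannot be ensured because children randomised to the control arm may display spontaneous movements and/or breathing" (Who will be blinded {17a}). Ancillary use is also a trial outcome in its own right; of the exploratory outcomes the article says "These include use of (non-) pulmonary ancillary treatment (e.g. steroids, inhaled drugs, prone positioning) and HFOV".

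**The concern.** Randomisation protects the comparison of arms against confounding by anything that precedes it. It gives no such protection once the model conditions on something the arm may have changed.

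**Ancillary treatment.** The background reports that "continuous administration of NMBAs significantly improved oxygenation in patients with moderate-to-severe PARDS", so an effect of rocuronium on the need for ancillary treatment is plausible. An imbalance would then be partly a treatment effect, and adjusting for it removes that part. Because sicker children are likely to receive more ancillary treatment, conditioning on it also makes the arms differ in unmeasured severity within each stratum of use. The rule brings the variable in exactly when the arms differ, which is when it is most likely to carry a treatment effect.

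**Parental perception.** It forms after allocation, when control children may visibly move or breathe, and the parents who hold it also complete the 14-item questionnaire. It may depend on the arm and on how the child fares.

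**Significance-based selection.** This clause makes the final model depend on data by arm. As worded it is not confined to baseline variables.

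At stake is whether the adjusted estimate still answers the intention-to-treat question, and whether the trial keeps its planned power.

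**Working it through.** **1. The plan's own figure.** Sample size {14} gives 74 per arm for a 20% difference, alpha 5% and power 80%, by t test, without a mean or SD. The figure therefore cannot be reproduced, only inverted (two-sided alpha assumed): d = (1.960 + 0.842) × √(2/74) = 0.46 SD. The implied SD-to-mean ratio is 0.20/0.46 = 0.43. I use d = 0.46 with 148 evaluable children.

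**2. Method for steps 3, 4b and 5.** Every input except 74 per arm and d is an assumption. Model: linear, outcome SD about 1, 4,000 simulated trials per scenario, arm effect estimated with and without the extra variable. A negative effect is benefit. Without the extra variable the estimate was about 0 under the null and about −0.46 at the design effect, with type I error near 5% and power 76 to 81%.

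**3. Ancillary treatment.** Severity U is standard normal with coefficient 0.5 on the outcome. The logit of use is 1.5U plus an arm term. Use is 50% in control. Ancillary treatment itself has a coefficient of 0 or 0.3 on the outcome, which gives the two ends of each range.

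| Use in active arm | Rule | Shift under null (SD) | Type I error | Estimate at −0.46 | Power |
|---|---|---|---|---|---|
| 50% | always adjust | about 0 | about 5% | −0.46 | 83% |
| 39% | always adjust | +0.06 to +0.09 | 7–9% | −0.41 to −0.38 | 72–67% |
| 39% | only if p<0.05 | +0.04 to +0.05 | 5–6% | −0.44 to −0.43 | 76–71% |
| 27% | always adjust | +0.12 to +0.19 | 11–22% | −0.34 to −0.27 | 52–36% |
| 27% | only if p<0.05 | +0.11 to +0.18 | 10–19% | −0.35 to −0.28 | 54–39% |

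If the arm does not affect use, nothing is lost. The p<0.05 trigger stands in for the article's undefined imbalance.

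**4. Parental perception.**

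(a) *Guess unrelated to outcome, correct with probability c in both arms.* Its correlation with arm is r = 2c − 1, and the effective size per arm is 74(1 − r²). At c = 0.8, r = 0.6 and 74 × 0.64 = 47.4, so power = Φ(0.46 × √(47.4/2) − 1.96) = 61%. For c = 0.6, 0.7 and 0.9, power is 78%, 73% and 39%. There is no bias.

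(b) *Guess dependent on arm and on the 12-month score* (logit = ±0.8 by arm − k × score, k = 0.5 or 1). The null shift is +0.17 or +0.27 SD and type I error 17% or 39%. The design effect shrinks to −0.27 or −0.12.

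(c) *Guess formed earlier, so that it depends on arm and severity but not on the 12-month score.* In a second set of scenarios (log odds ratio 1 to 2 for arm, 0.5 to 1 per SD), the null shift was 0.06 to 0.20 SD and the adjusted effect 0.39 to 0.26 SD. With the same coefficients applied to the outcome itself, the figures were 0.11 to 0.33 SD and 0.33 to 0.06 SD. Recording the guess early reduces the problem but does not remove it.

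**5. Covariates picked by significance.** Ten independent baseline covariates, each with coefficient 0.25, kept only if p<0.05 between arms: estimate 0.003 under the null and −0.466 against a true −0.464, so no bias. Type I error was 3.3%. Power was 83%, against 99% with all ten pre-specified.

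**6. Side by side.** The endpoint definition is adjusted, with one list. The regression in {20a} uses another. The sample size rests on an unadjusted t test, which {20a} also plans. The article does not say which result decides the trial.

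**The case against.** The strongest reply is that an unadjusted test of the primary outcome is also planned, and the trial is sized on it, so a clean randomised comparison will exist whatever the regression does. That stands, and a reader should not infer that the trial's only comparison is compromised. It does not dispose of the point, because the endpoint is defined as adjusted and the decisive analysis is not named.

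Second, the ancillary adjustment is conditional. That also stands: with use at 39% against 50% the conditional rule is nearly harmless. With 27% it is not.

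Third, a reader might infer that the bias must run towards no effect or apparent harm. The article does not support this. It reports better oxygenation under neuromuscular blockade but no effect on ancillary use. Its Discussion notes that such agents were used more often alongside inhaled nitric oxide and HFOV, an observational pattern that may reflect severity. If rocuronium raised ancillary use, the bias would reverse: in a separate linear scenario, with the odds of use multiplied by exp(0.5) = 1.6 or exp(1) = 2.7, the adjusted benefit rose from 0.46 to about 0.52 or 0.57 SD.

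Fourth, it is tempting to treat the parents' guess as a consequence of the outcome. The article does not say when perception is recorded. If that is before month 12, the 12-month score cannot cause it, and the larger figures in step 4(b) do not apply.

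Fifth, a reader might add significance-selected covariates to the sources of bias. Step 5 shows that this does not follow for true baseline variables.

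Lastly, the simulations are linear, whereas the plan is zero-inflated regression on a 14-item score. They show mechanism and rough scale only.

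**Conclusion.** The concern holds as a risk built into a stated adjustment rule, not as a demonstrated bias. Two of the planned adjustment variables arise after randomisation, one of them is itself a trial outcome, and neither is in the article's own definition of the adjusted endpoint. Bias requires that the arm affects the variable and that the variable is linked to the outcome or to unmeasured severity. Both conditions are plausible here; neither is established, and the direction is open.

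Under the assumed inputs the consequences run from nothing to substantial. At the upper end of the ancillary scenarios, the effect falls from 0.46 to about 0.27 to 0.34 SD if the model always adjusts, and type I error is 10 to 19% under the conditional rule. A guess tied to arm and current symptoms shifts the null by 0.17 to 0.27 SD, and by less if recorded earlier. A guess unrelated to outcome only costs power. The significance clause is a matter of an unfixed model and lost precision, except that its wording could let in further post-randomisation variables.

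**What to change.** 1. In {20a}, name the single analysis that decides the primary outcome, and make it agree with the Primary outcome measure paragraph and with the t test behind the sample size.
2. If that analysis is the adjusted model, give one fixed, pre-specified list of covariates that the arm cannot affect, identical in both sections. Settle whether day-care belongs on it.
3. Delete from that model parental perception, ancillary treatment and the clause on variables that differ significantly between arms.
4. Report ancillary treatment by arm as the exploratory outcome it already is.
5. Report parental perception by arm as a description of blinding, and state when it is recorded. Any model adjusted for it, or for ancillary use, should be labelled exploratory.

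The cost is wording only. The same data are collected and reported, and the sample size and conduct of the trial do not change. In the simulations, leaving out the post-randomisation variables kept the estimate unbiased, with type I error near 5% and power near 80%.

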#### Secondary outcomes

For the secondary outcome measures, repeated measures will be tested using generalised estimating equations (GEE), adjusting for the outcome of randomisation and time and any other confounding factors applicable to the outcome measure. Non-repeated continuous measures will be compared between using either the Student *t* test or the Mann-Whitney *U* test, non-repeated dichotomous variables will be tested using the Chi-squared test or the Fisher Exact test if the absolute value is below 5. They will be displayed as a percentage (%) of the total with a 95% confidence interval.

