### Objectives {7}

The primary objective is to test the hypothesis that the use of NMBAs for 48 h in paediatric patients younger than 5 years of age with early moderate-to-severe PARDS will lead to at least a 20% reduction in cumulative respiratory morbidity score 12 months after discharge from the PICU.

The secondary objectives are to evaluate the effects of NMBAs on pulmonary and systemic inflammation, metrics for oxygenation and ventilation, non-respiratory organ dysfunction, and respiratory system mechanics.

Exploratory objectives: ventilator free days (VFD) at day 28, PICU and hospital length of stay, 90-day mortality, concomitant use of sedatives, complications (e.g. adverse drug reactions, reintubation rate, critical illness polyneuropathy and myopathy, ventilator-associated pneumonia (VAP), withdrawal syndrome, delirium), the course of the respiratory morbidity score at 3, 6 and 9 months and lung function (lung clearance index (LCI), functional residual capacity (FRC).

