#### Secondary outcome measures

Secondary outcomes include LCI and FRC measured using multiple breath wash-out 12 months after PICU discharge, and the level and time course of the cumulative respiratory morbidity score assessed at baseline, 3, 6 and 9 months after PICU discharge. Secondary outcome measures related to the acute phase of disease (i.e., during PICU admission) include level and time course of ventilator settings (peak inspiratory pressure, plateau pressure, mean airway pressure, driving pressure, PEEP, set rate, total rate, inspiratory time), respiratory system mechanics (quasistatic compliance, dynamic compliance, respiratory system resistance), metrics of oxygenation (SpO_2_/FiO_2_ ratio, PaO_2_/FiO_2_ ratio, OI, OSI) and ventilation (PCO_2_, pH), and hemodynamic parameters (heart rate, blood pressure, central venous pressure, daily cumulative fluid balance, number of fluid challenges). We will measure the level and time course of the non-respiratory pediatric logistic organ dysfunction 2 (PELOD – 2) score as measure of organ dysfunction and pediatric Risk, Injury, Failure, End-stage renal failure (pRIFLE) criteria for acute kidney injury, the number of adverse drug reactions, and re-intubations [27, 28]. We will study the level and time course of the pulmonary and systemic inflammatory response, the prevalence of critical illness polyneuropathy and myopathy, and ventilator-associated pneumonia.

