### Sample size {14}

The primary outcome is the cumulative respiratory morbidity score 12 months after PICU discharge. A classical sample size based on a independent sample *t* test between two groups was calculated, assuming a 20% difference in cumulative mean respiratory morbidity score. This resulted in a required sample size of 148 patients (*N* = 74 intervention versus *N* = 74 placebo) to demonstrate a 20% reduction in respiratory symptoms in the intervention group compared to the placebo with an alpha of 5% and power of 80%. Considering a potential maximum drop-out of 20% per group because of withdrawal of consent or loss to follow-up, we need to enrol *N* = 89 patients per group. Thus, the total sample size is 178 patients.

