## Data collection and management and storage of biological specimens

### Plans for assessment and collection of outcomes {18a}

#### Primary outcome

The respiratory morbidity will be assessed using a structured questionnaire in agreement with recommendations from the American Thoracic Society [29]. This parental questionnaire studies the presence of respiratory symptoms including cough, wheezing and shortness of breath during rest and/or activity. The questionnaire consists of 14 items that can only be answered by yes or no. The questionnaire is commonly used and validity of the items in the respiratory morbidity score has been shown [29, 30]. Upon discharge, parents or legal caretakers are asked for their e-mail address and phone number; the personalised link to the web-based questionnaire will be e-mailed to them 12 months after PICU discharge. If there is no response within 7 days, they will receive a reminder via e-mail. The questionnaire is personalised and anonymised. The same questionnaire is used upon PICU admission to study baseline respiratory morbidity.

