Assessment of the level and time course of the cumulative respiratory morbidity score assessed at baseline, 3, 6 and 9 months after PICU discharge will be done using the same questionnaire as described above. LCI and FRC will be measured 12 months after PICU discharge using multiple breath washout techniques [33]. Such lung function testing is feasible and validated, even in small children. Testing will be performed by dedicated paediatric pulmonology function testing technicians in participating centres that are equipped with this technique.

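### The GEE for repeated secondary outcomes names no arm-by-time term although time course is the outcome, and it is unclear whether the baseline respiratory score is an outcome or a covariate

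*Protocol article*

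**What the plan says.** The protocol article, under Statistical methods, Secondary outcomes, gives one model for every repeated secondary measure: "repeated measures will be tested using generalised estimating equations (GEE), adjusting for the outcome of randomisation and time". The adjustment clause in full is "adjusting for the outcome of randomisation and time and any other confounding factors applicable to the outcome measure". Arm and time are named and the confounders are left open. No arm-by-time interaction is named, and nothing says how a baseline value enters.

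The Secondary outcome measures section defines the repeated outcomes by their level and their time course. This covers ventilator settings, respiratory mechanics, oxygenation and ventilation, haemodynamics, organ dysfunction and inflammation ("We will study the level and time course of the pulmonary and systemic inflammatory response"). For the questionnaire score it names "the level and time course of the cumulative respiratory morbidity score assessed at baseline, 3, 6 and 9 months after PICU discharge". The data-collection section repeats those four points: "Assessment of the level and time course of the cumulative respiratory morbidity score assessed at baseline, 3, 6 and 9 months". The Objectives section lists the same item as exploratory and without baseline: "the course of the respiratory morbidity score at 3, 6 and 9 months". On the timing of baseline, the article says: "The same questionnaire is used upon PICU admission to study baseline respiratory morbidity".

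**The concern.** There are two problems of different strength.

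The first concerns all repeated series. A model with main effects for arm and time assumes that the two arms run parallel. Its arm coefficient speaks to level. It has no parameter for a difference in course, which is half of the stated outcome. An effect that fades after a 48-h infusion is plausible, and this model would report it as a small average.

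The second concerns the respiratory score and is conditional. The admission questionnaire precedes treatment, so its expected arm difference is zero under randomisation. If it is one of the modelled outcomes under a single arm term, that known zero is averaged into the effect. The estimate shrinks and power falls, although the same baseline value used as a covariate would add precision.

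**Working it through.** The article gives no figure for the GEE, so there is none to reproduce.

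**Inputs**
- From the article: 74 per arm, alpha 5% (taken as two-sided), power 80% (Sample size); four time points (Secondary outcome measures).
- Assumed: an effect constant over follow-up, equal variances, complete data, and exchangeable within-child correlation r of 0.3, 0.5 or 0.7.
- Effect size: the sample size section gives only a relative target ("assuming a 20% difference in cumulative mean respiratory morbidity score"), without mean or SD. Back-solving from 74 per arm gives d = (1.96 + 0.84) × √(2/74) = 0.46 SD. That figure belongs to the primary outcome and is borrowed here. A smaller 0.3 SD is shown beside it.

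**Dilution, if baseline is one of four outcomes**

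With complete data and an independence or exchangeable working correlation, the arm coefficient in an arm-plus-time GEE is the mean of the arm differences over all visits: (0 + d + d + d)/4 = 0.75d. For d = 0.46 that is 0.345.

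**Power**

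Power = Φ(d × √(74/2) × k / √v − 1.96), where
- baseline as a fourth outcome: k = 0.75, v = (1 + 3r)/4
- post-baseline visits only: k = 1, v = (1 + 2r)/3
- post-baseline visits with baseline as covariate: k = 1, v = (1 + 2r)/3 − r²

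At r = 0.5 the variances are 0.625, 0.667 and 0.417. For d = 0.46, d√37 = 2.798, so the first case gives Φ(2.798 × 0.75/0.791 − 1.96) = Φ(0.69) = 76%, and the third gives Φ(2.798/0.645 − 1.96) = Φ(2.38) = 99%.

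| d | r | baseline as outcome | post-baseline only | baseline as covariate |
|---|---|---|---|---|
| 0.46 | 0.3 | 86% | 97% | 99% |
| 0.46 | 0.5 | 76% | 93% | 99% |
| 0.46 | 0.7 | 66% | 88% | >99% |
| 0.3 | 0.3 | 51% | 70% | 78% |
| 0.3 | 0.5 | 41% | 61% | 81% |
| 0.3 | 0.7 | 34% | 53% | 91% |

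A GEE simulation (200 runs, 74 per arm, r = 0.5, true effect 0.46) agrees: mean arm coefficient 0.349 and power 76% with baseline as an outcome, against 0.455 and 99.5% with baseline as a covariate. If 20% of children have a baseline score only, the first coefficient falls further, to 0.29 (exchangeable) or 0.31 (independence), with power 57% or 62%.

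**Time course**

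In the same simulation, with baseline among the four outcomes:
- Arm differences of 0.46, 0 and −0.46 SD at 3, 6 and 9 months: the arm term rejects in 5.5% of runs, and a 3-df arm-by-time test in 99.5%.
- Fading differences of 0.6, 0.3 and 0 SD: 38% and 96%.

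The 3-df test also picks up the change from baseline. Over the three post-baseline visits alone the test has 2 df, with noncentrality (74/2) × Σ(dₜ − d̄)²/(1 − r). For the fading pattern this is 37 × 0.18/0.5 = 13.3, giving power of about 92%. For the crossing pattern it is 37 × 0.4232/0.5 = 31.3, giving more than 99%. So the course remains testable in the model proposed under the fix.

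**The case against.** The strongest reply is that this is one sentence in a condensed article. GEE terms for secondary outcomes are often left to the analysis plan, and the sentence does not exclude an interaction. That limits the conclusion to this text, and a reader should not infer that the trial will be unable to test time course. It does not remove the point, because the sentence does name the terms, and they do not match the outcome definition.

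It would also be wrong to say that the model holds arm and time alone. The sentence goes on to admit other confounding factors, and the baseline score could enter there. The article does not say that it does: its confounder lists for the same score at 12 months omit it, and baseline appears there only in a separate paired comparison. Nor can that clause supply the interaction, since an arm-by-time term is not a confounder.

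A reader might take the 3/4 dilution as established. It is not. The lists with baseline may be collection schedules, and under the objectives' wording, without baseline, the dilution disappears. A reader might also extend it to the ventilator, oxygenation and inflammation series. The article text gives no sampling times for these, and the schedule table is not shown, so a pre-dose value in those models cannot be established.

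Finally, the power figures rest on chosen inputs. At 0.3 SD alone the loss would look worse than at the effect implied by the article's own sample size, so both are given. The dilution does not inflate type I error.

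**Conclusion.** The point stands in a limited form, for secondary outcomes. The named terms cannot test a difference in time course, although the article makes time course an outcome for every repeated series. This part needs no numerical assumption.

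For the respiratory score the article's sections disagree on whether baseline belongs to the series, and the model sentence does not settle its role. If it is a fourth outcome under one arm term, a constant effect is estimated 25% too small. At r = 0.5 and 74 per arm, power is 76% against 99% (0.46 SD) or 41% against 81% (0.3 SD), compared with using baseline as a covariate. These sizes rest on the assumed effect, its constancy, exchangeable correlation and complete data. The 12-month primary analysis is a separate model and is not touched.

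**What to change.** 1. Reconcile the Objectives, Secondary outcome measures and data-collection sections on whether baseline is part of the repeated respiratory score.
2. Use post-baseline values as outcomes, with the baseline value as a covariate wherever one is collected.
3. Include arm, time and arm-by-time. Report the average post-baseline arm difference for level and the interaction test for time course.

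Keeping baseline as an outcome with arm-by-time terms is also accepted practice. What should be avoided is baseline as an outcome under a single arm term.

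The cost is a change of model terms and a few sentences of text, made before unblinding. The baseline questionnaire is already collected, so no new data are needed.
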